### Power calculation

We will include 220 elderly in both the experimental and control group. We expect a 10% loss to follow-up (due to mortality, re-housing, impossibility or unwillingness to participate further) between inclusion and T1 and a 20% loss between T1 and T2. The sample is sufficient to detect changes in our primary measure of quality of life. Assuming an average effect size of 0.5 and significance of 5%, this gives a power of 0.997. If we assume a small effect size of 0.3 with a significance of 5%, this still supplies sufficient power at 0.837. Interfering variables will also play a role. At an average effect size (f2) of 0.15 and significance of 5%, assuming five independent variables, the power is 0.97. Even with 15 independent variables, the power remains sufficient at 0.856.

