### Data analysis

The experimental and control groups will be described at every point in time with descriptive statistics. Similarity of characteristics between the two groups will be assessed with t-tests, chi-square tests, and Fisher’s exact tests. Bivariate analyses and regressions with the demographic characteristics will determine multicollinearity and correlations with the process and outcome measures. All analyses will be controlled for differences in baseline characteristics and demographic characteristics. For the self-constructed questionnaires, factor analyses and reliability analyses will be performed to determine construct validity. To determine changes over time, t-tests will be performed for each process and outcome measure. For each measure, regression analyses will be performed with the T2-score as the dependent variable and the T0-score, the research group (experimental or control), and demographic variables as independent variables. With subgroup analyses, potential variation between study results between subgroups will be analyzed.

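### The regression powers of 0.97 and 0.856 belong to the overall R-squared test at one group's size, not to the research-group term that estimates the WICM effect

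*Protocol article*

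**What the plan says.** The Power calculation section sets the size: "We will include 220 elderly in both the experimental and control group", with a 10% loss "between inclusion and T1 and a 20% loss between T1 and T2". It then gives two powers for a two-group difference: "Assuming an average effect size of 0.5 and significance of 5%, this gives a power of 0.997", and "If we assume a small effect size of 0.3 with a significance of 5%, this still supplies sufficient power at 0.837".

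After remarking that other variables will interfere, it turns to regression: "At an average effect size (f2) of 0.15 and significance of 5%, assuming five independent variables, the power is 0.97". It adds: "Even with 15 independent variables, the power remains sufficient at 0.856". Neither sentence names the hypothesis tested or the number of people in the regression.

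The Data analysis section describes the model used for each measure, with "the T2-score as the dependent variable and the T0-score, the research group (experimental or control), and demographic variables as independent variables". The WICM effect in that model is one coefficient, and the model can only be fitted to both groups together.

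**The concern.** The two regression figures are offered as assurance that adjustment for other variables leaves enough power. A reader will take them as the power to detect the WICM effect in the adjusted model. Yet power that falls from 0.97 to 0.856 as predictors rise from 5 to 15 is typical of a joint test of all predictors. A test of one coefficient loses only a few residual degrees of freedom when predictors are added.

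If the figures are for the joint test, they answer whether the predictors as a set explain any of the T2-score. A baseline score that predicts its own follow-up is enough to make that true. The adjusted between-group comparison would then have no stated power, although the section appears to give one.

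**Working it through.** **Inputs.** From Power calculation: 220 per group, losses of 10% and 20%, 5% significance, f2 = 0.15, 5 or 15 predictors, d = 0.5 and 0.3. From Data analysis: the model and its research-group term. The T0-T2 correlation r is not in the document and is treated as an assumption over a range.

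**Retained numbers.** Losses added: 220 × 0.70 = 154 per group, 308 in total. Losses compounded: 220 × 0.90 × 0.80 = 158.4, so 158 per group and 316 in total.

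**Reproducing the stated figures.** For the overall test with u predictors, the noncentral F has df1 = u, df2 = N − u − 1 and noncentrality λ = f2 × N. At N = 154, λ = 0.15 × 154 = 23.1.

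| Total N | 5 predictors | 15 predictors |
|---|---|---|
| 154 | 0.9712 | 0.8562 |
| 158 | 0.975 | 0.868 |
| 220 | 0.998 | 0.972 |
| 308 | 0.9999 | 0.998 |
| stated | 0.97 | 0.856 |

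Of these sizes only N = 154 matches both figures to the printed digits. That 154 is one group's size is supported by the two-group sentences: a one-sided t-test with 154 per group gives 0.9969 and 0.8369, which are the printed 0.997 and 0.837.

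**Could they be powers of the group term?** For a single coefficient, df1 = 1 and df2 = N − p − 1, with p predictors in the model. At N = 154 and f2 = 0.15, power is 0.9976 with 5 predictors and 0.9975 with 15. Matching 0.97 would need N of about 100, and matching 0.856 would need 63 to 64. No common N gives both.

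**What f2 = 0.15 requires.** R-squared = 0.15 / 1.15 = 0.130. A T0-T2 correlation of √0.130 = 0.36 supplies that with a WICM effect of zero (an illustration, since the protocol gives no correlation). The overall test would still have its stated power.

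**Power of the group term.** For equal groups, with d on the unadjusted SD scale, partial f2 = d² / [4(1 − R²)], where R² is the share of within-group outcome variance explained by the covariates. Here R² is taken as r², and the test is two-sided at 5% with N = 308. For d = 0.3 and r = 0: f2 = 0.09 / 4 = 0.0225 and λ = 0.0225 × 308 = 6.93. For d = 0.3 and r = 0.5: f2 = 0.0225 / 0.75 = 0.0300 and λ = 9.24.

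| Assumed r | d = 0.3 | d = 0.5 |
|---|---|---|
| 0 | 0.747 | 0.992 |
| 0.3 | 0.785 | above 0.992 |
| 0.5 | 0.858 | above 0.992 |
| 0.7 | 0.957 | above 0.992 |

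These agree to within 0.001 for 5 and 15 covariates. For d = 0.3, power reaches 0.80 at r of about 0.36 (0.803 there). At N = 316 and r = 0 the d = 0.3 figure is 0.757.

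**The case against.** The strongest reply is that the practical conclusion survives. At d = 0.5, which the protocol calls average, the group term has power of at least 0.992 with 5 or 15 covariates. Extra covariates cost almost nothing, and using one group's size made the overall-test figures lower than they would be with both groups (0.9999 and 0.998). All of this stands. The error in N is conservative, and the substantive fault is the hypothesis.

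The test and N are also inferred, because the section names neither. The inference is firm, since one test at one N gives both printed values and a single-coefficient test cannot.

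Three stronger readings are tempting but not supported:

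- A reader might infer that the adjusted analysis is underpowered. At d = 0.5 it is not. At d = 0.3 the answer depends on a correlation that the document does not give, and 0.747 is only the zero-correlation end of the range.
- A reader might blame this error for the gap between the printed 0.837 and 0.747 at d = 0.3. That gap arises because 0.837 is a one-sided figure; it belongs to a different sentence.
- A reader might infer that the plan assumes an intervention effect of d = 2 × √0.15 = 0.77. That conversion applies only if f2 is the effect of group alone. As the joint effect of all predictors, f2 = 0.15 corresponds to no particular d.

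**Conclusion.** The concern holds in this limited form. The printed 0.97 and 0.856 are correctly computed for an overall R-squared test with 154 people, but the planned analysis tests one research-group coefficient with about 308 to 316. They give no information on the power to detect a WICM effect after adjustment.

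On the protocol's own effect sizes, the group term is well powered at d = 0.5. At d = 0.3 its power lies between 0.747 and 0.957 for assumed correlations from 0 to 0.7, so calling it sufficient there depends on a correlation of about 0.36 or more.

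These figures assume equal groups, independent observations, and a research-group variable uncorrelated with the covariates. Clustering by practice was not assessed here. Because groups are not randomised, any correlation between group and covariates would lower the power somewhat.

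**What to change.** Replace the two sentences built on f2 = 0.15 with the power of the two-sided, one-degree-of-freedom test of research group in the T0-adjusted model. Use both groups after loss, the section's own d = 0.5 and d = 0.3, and partial f2 = d² / [4(1 − R²)]. State the assumed T0-T2 correlation and its source, or show a range such as the one above. Name the test, its sidedness and the total N, so that the figure can be checked.

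Using d²/4 together with a T0-T2 correlation would be inconsistent, because d²/4 applies only when covariates explain nothing.

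The cost is two sentences in the power section. Recruitment, measurements and conduct do not change.

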### Study sample: sampling and eligibility criteria

Sampling will take place at GP practices in Walcheren. The experimental group will consist of the elderly patients of 8 GPs from 3 GP practices located in the east of Walcheren who will provide care according to the WICM. The control group will consist of 6 GPs from 5 GP practices in the north, south, and west of Walcheren who will provide traditional care. All elderly aged 75+ years in these practices who live independently will be asked to complete the GFI, along with several demographic questions and a consent form. Approximately 900 elderly in both the experimental and control practices will be contacted. The questionnaire is accompanied by a letter from the GP to raise the likelihood of response and assure that the elderly are well informed. After being sent a reminder, the elderly will be contacted by telephone or visited at home to be asked to participate and to help complete the questionnaire if necessary. These activities are expected to result in an 80% response rate. Elderly will be included if they score ≥4 on the GFI, if they have signed the consent form, or if they are able to make that decision themselves. Exclusion criteria are as follows: elderly on a waiting list for a nursing home, elderly who are not able to decide themselves if they want to participate (e.g., in case of dementia), and elderly with a life expectancy of <6 months due to a terminal illness. Included elderly will be asked to provide contact information for their informal caregiver. The caregivers will be contacted either by telephone or face-to-face during the first visit from the researchers at the home of the elderly subjects. They will be asked to fill in a written consent form if they agree to participate. Non-respondents will be contacted again by telephone. A response rate of 60% is expected. Health professionals will be selected based on their function and region of employment. An estimated 400 questionnaires will be sent to health professionals in the experimental and control groups. We expect a response rate of 50%.

### Data collection and instruments: frail elderly

Outcome data and data on demographics (age, sex, living arrangement, education, and marital status) will be collected with questionnaires and file research at three points in time: T0, T1 (3 months after inclusion), and T2 (12 months after inclusion). Research has shown that effects can be expected 3 months after starting to use the EASYcare instrument [41]. The T2 measurement takes place to determine long-term effects. All elderly will be visited at home by trained interviewers recruited from the region of Walcheren to ensure a cultural fit with the elder. Interviewers will have a background in healthcare to ensure a high-quality interview. Every elder will be given a gift at T1 as a token of appreciation and to motivate further participation. File research will occur at the GP practices. The following instruments will be used (see Table 1):

#### Perceived health

##### SF-36

The SF-36 measures eight concepts: physical functioning, bodily pain, role limitations due to physical, personal, and emotional health problems, emotional well-being, social functioning, energy/fatigue, and general health perceptions [42,43]. The items regarding perceived current health and changes in health will be used.

#### Social functioning

##### SF-36

The SF-36 question on social functioning ‘During the past 4 weeks, to what extent has your physical health or emotional problems interfered with your normal social activities with family, friends, neighbors, or groups?’ will be used.

#### Mental wellbeing

##### SF-36

The 5-items scale on emotional wellbeing from the SF-36 will be used.

#### Quality of life

##### ICECAP

The ICECAP instrument was developed for elderly and measures their quality of life using the following 5 dimension on the capacity to perform certain actions and achieve certain states: attachment, security, role, enjoyment, and control. Each dimension consists of one question that can be scored on four levels [44].

##### EQ-6d

The EuroQol (EQ6D) is used to measure quality of life in terms of valued health and is composed of the dimensions mobility, self-care, usual activities, pain/discomfort, anxiety/depression, and cognitive functioning [45,46]. Each dimension is scored on three levels: ‘no problems,’ ‘some problems,’ and ‘severe problems.’ The EQ-6d will also be used to calculate cost-utilities of health care.

##### SF-36

Questions based on the SF-36 on perceived current quality of life and the quality of life compared with one year ago will be used.

##### Cantril’s self-anchoring ladder

Perceived quality of life will be measured with the Cantril’s ladder, a measurement technique that asks subjects to mark their satisfaction with life from 0 to 10 [47].

#### Physical functioning

##### KATZ-15

The Katz-15 will be administered to measure physical functioning by means of 15 yes or no questions covering domains of activities of daily functioning, such as bathing, transferring, eating, and dressing [48,49].

#### Health care use

##### Questions on self-reported use

Use of healthcare will be measured with 16 questions regarding the use of seven domains of care (hospital admissions, unplanned care, respite care, medical, paramedic, psychosocial care, and daycare). Elderly will be asked if they make use of care, and if so, how often (in days or hours depending on the type of care).

##### File research

The files of the elderly from the GPs will be analyzed regarding health care use. Data will be collected on the same domains as described above and compared with self-reported use.

### Data collection and instruments: caregivers

Outcome data and demographic data (e.g., age, sex, income, relationship, and living with loved one) from the caregivers will be collected with questionnaires at three time points: T0, T1 (3 months after inclusion), and T2 (12 months after inclusion). Caregivers will be sent a questionnaire or interviewed at the same time as the elder at their home. Caregivers will also be given a gift at T1. The questionnaire is composed of the following instruments (see Table 2):

#### Perceived health

##### SF-36s

As for the elderly, the items on perceived current health and changes in health from the SF-36 health survey will be used.

#### Objective burden

##### Short version Erasmus iBMG instrument “objective burden informal care

This instrument measures and divides the time spent on the elderly into the following domains: household tasks, personal care, help with moving and contacts with family, friends and health care providers, and medical technical tasks [50]. Caregivers will be asked if they give help, and if so, how many hours per week.

#### Subjective burden

##### Carer‒Qol

The CarerQol will be used to measure the impact of informal care [51,52]. The CarerQol-VAS assesses happiness with a horizontal Visual Analogue Scale (VAS) with 0 (‘completely unhappy’) and 10 (‘completely happy’) as endpoints. The CarerQol-7d describes seven dimensions of burden: fulfillment, support, relational and mental health problems, problems with combining daily activities, finances, and physical health. The answer categories are ‘no’, ‘some’ and ‘a lot of problems.’

##### Self-related burden VAS (SRB)

The SRB will be used to measure the overall perceived burden. The SRB asks how straining the care for the loved one is with a horizontal VAS ranging from 0 (‘not straining at all’) to 10 (‘much too straining’) [53].

##### Caregiver Strain Index+ (CSI+)

The CSI+ will be used to measure perceived strain. The CSI+ is an extended version of the 13-item instrument CSI, which only measures negative dimensions of the caregiver situation. The CSI+ adds 5 items on positive dimensions covering the areas of patient characteristics, subjective perceptions of the care-taking relationship by caregivers, and emotional health of caregivers [54,55].

##### Question on perseverance time

The question of how long the caregiver anticipates being able to pursue his tasks as a caregiver will be asked, with answers ranging from less than two weeks to more than two years [56].

##### Assessment of the informal care situation (ASIS)

To assess the desirability of the caregiving situation, the ASIS will be used, which is a horizontal VAS ranging from 0 (‘worst imaginable caregiving situation’) to 10 (‘best imaginable caregiving situation’) [51].

#### Quality of life

The same *SF-36* based questions and Cantril’s self-anchoring ladder for the elderly will be used.

#### Use of community services

##### Community Service Attitude Inventory (CSAI)

The CSAI is a 25-item Likert-type scale that will be used to measure the attitude and willingness of caregivers toward the use of community services [57].

##### Survey question

Caregivers will be asked if they use community services.

### Data collection and instruments: health professionals

Data on the outcomes will be collected from GPs, nursing home doctors, geriatrists, geriatric nurse practitioners, secondary line geriatric nursing specialists, specialists in hospitals, home care employees, mental health professionals, and paramedical specialties with the following instruments (see Table 3):

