Changes also occur in the attitudes of the elderly toward care. These changes also necessitate changes in the organization of care. The frail elderly no longer silently accept the care that they are given and now demand their care meets their needs. Patient-centeredness has become a legitimating base for healthcare provision and has been reinforced by laws that strengthen patient's rights. These laws also force providers to provide the care that the elderly want and need at the right time and place [5,18-20]. A supply-oriented approach and the fragmentation in the organization of the elderly care today inhibit progress on this issue. Service is still often characterized by a lack of continuity and coordination on the behalf of involved providers. Responsibility for the whole continuum of care is absent and results in inefficient and ineffective care [21,22]. The specific needs of the frail elderly and their caregivers, budget restraints and patient-centered views call for new and more effective organizational structures.

The integration of health services and social services for the frail elderly has gained tremendous attention as a means to accomplish this. There is a widespread belief that the integration of these will enhance satisfaction, quality of life, efficiency, and health outcomes and will also decrease costs [23-26]. The rationale behind this stems from the fact that a single service provider is usually unable to respond to all the needs. This prohibits efficiency in the delivery process. To meet the multiple needs of the frail elderly in an efficient and effective manner, some claim that numerous service providers will need to combine their efforts in a coordinated manner [27-29]. There is also mounting evidence that confirms beliefs that the development of integrated care arrangements can be cost effective and enhance quality [30-38].

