Though widely acknowledged and pursued, the implementation and evaluation of integrated services for the frail elderly has not yet reached its full potential. Much is still unknown regarding how services can be integrated and the effects of integration. In this study, a new integrated model for the frail elderly, the Walcheren Integrated Care Model, will be developed and evaluated. Walcheren refers to the region in the Netherlands where the study takes place. The Walcheren Integrated Care Model is in accordance with scientific evidence and addresses the design elements that affect the quality of care. It has an umbrella organizational structure involving case management, multidisciplinary teams, protocols, consultations, and patient files. It will be an organized provider network with evidence-based needs assessments [29,32,33]. All elements are embedded in the model. However, more types of health professionals participate in the model than other studies have previously investigated. General practitioners, geriatricians, home health care workers, paramedics, social workers, pharmacists, and mental health care professionals all take part in the designed model. In contrast with other models, this model also contains a preventive element: a screening tool to detect frailty in the elderly. Finally, the model is being evaluated on a broader range to obtain a comprehensive evaluation and determine possible trade-offs between effects.

This article describes the study design of the evaluation of the Walcheren Integrated Care Model compared with traditional care. The development and evaluation of the model are part of the National Care for the Elderly Program (NPO), which is funded by the Netherlands Organization for Health Research and Development (ZonMW; project number 313030201).

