The proposed plan is then discussed in a multidisciplinary meeting led by the GP. Depending on treatment goals, the meeting is also attended by other health professionals who may be needed. During the meeting, a multidisciplinary care plan will be approved, actions and care paths will be discussed, and agreements will be made about the care to be deployed and the activities of all persons involved. The treatment plans of each professional are included in the care plan. The GP harmonizes the care plan with the elderly and their caregiver and obtains permission for its implementation. A chain computerization system accessible by the health professionals involved will be used for the multidisciplinary care plan. The professionals will automatically receive an email in the event of changes in use of care or a transfer.

The case manager is responsible for admittance to the required services, the planning and coordination of care delivery, and periodical evaluation of the care plan. Thus, the case manager arranges obligatory need assessment, monitors the elderly at least every six months for one year, and supports the multidisciplinary team by arranging meetings and streamlining the necessary exchange of information. The responsibilities and activities of the involved professionals and case manager are formalized in agreed protocols with predefined modes of referral and collaboration. During the process, the GP practice functions as a single entry point. It is the gate through which elderly and professionals can access the expertise and services of all health and social care professionals and organizations. The GP and case manager work in close collaboration to ensure timely and correct care assessment and provision. To be able to fulfill their tasks, the GPs must have completed an executive training in geriatric care, a course in GP consults and EASYcare training. The case managers must have successfully attended the EASYcare training and a course in case management.

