#### Degree of integration

##### Questionnaire

To determine the degree of coherence, continuity, and co-operation, a questionnaire will be developed based on a systematic review of integration indicators and instruments for measuring integration. The questions will be part of the questionnaire sent to the health professionals as described above. Health professionals are again asked to assess the current levels of integration and those 18 months previously.

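### Social workers and pharmacists take part in the model but are not on the list of surveyed professionals, so as written the mailed integration ratings include neither group

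*Protocol article*

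**What the plan says.** The Background presents the breadth of professions as a feature that sets this model apart from those studied before, and names them: "General practitioners, geriatricians, home health care workers, paramedics, social workers, pharmacists, and mental health care professionals all take part in the designed model". It also gives the rationale for the work: "The integration of health services and social services for the frail elderly has gained tremendous attention as a means to accomplish this". The description of the intervention makes the GP practice a single entry point through which users can "access the expertise and services of all health and social care professionals and organizations".

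The section on data collection from health professionals states who is surveyed. It begins "Data on the outcomes will be collected from GPs, nursing home doctors, geriatrists, geriatric nurse practitioners, secondary line geriatric nursing specialists" and continues "specialists in hospitals, home care employees, mental health professionals, and paramedical specialties with the following instruments". Nothing in the sentence marks the list as examples.

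For the degree of integration, the process-indicator section says: "The questions will be part of the questionnaire sent to the health professionals as described above". Table 4 gives one instrument for that measure, a self-constructed mailed questionnaire. It lists the relational coordination survey, also mailed, under satisfaction of health professionals.

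**The concern.** The research question under Aim asks about effects on health professionals and on the organization of care. The degree-of-integration measure is the quantitative evidence on the second of these, and the model sets out to join health services with social services.

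A tie between two sectors has two ends. If only GPs, medical specialists, nurses, home care, mental health and paramedical staff answer, the summary score can rise because these groups work better with one another. The score would carry no view from social work on whether its own link to the GP practice improved. The same holds for pharmacy. The omission also leaves both groups out of the mailed measures of knowledge, job satisfaction and subjective burden in Table 3.

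**Working it through.** No power or sample-size formula applies. The check sets the two lists side by side and then traces the integration questionnaire back to its recipients.

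**Step 1: match the lists.**

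| Takes part in the model (Background) | Counterpart among those who supply data |
|---|---|
| General practitioners | GPs |
| Geriatricians | Geriatrists |
| Home health care workers | Home care employees |
| Paramedics | Paramedical specialties |
| Mental health care professionals | Mental health professionals |
| Social workers | none |
| Pharmacists | none |

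Seven groups are named; five are matched and 7 − 5 = 2 are not. The data-collection list has nine entries. Its other four are nursing home doctors, two geriatric nursing roles and hospital specialists. None is a social-work or pharmacy profession.

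**Step 2: could the missing groups sit inside another entry?** The Background names social workers separately from home care and mental health workers, and pharmacists separately from paramedics. In the article's own terms these are distinct groups. The Background also calls all seven health professionals, so limiting the survey to health professionals does not explain the omission.

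**Step 3: trace the instruments.** The degree-of-integration questions belong to the questionnaire already described for health professionals, and Table 4 gives no other source for that measure. The relational coordination survey is likewise a mailed questionnaire about relations between health professionals. The article gives no separate mailing list for it, so I take it to go to the same people.

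**Step 4: what else is lost, and what is not.**

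- Knowledge, job satisfaction and subjective burden come only from the mailed questionnaire (Table 3), so neither group contributes.
- Objective burden has further sources: care use reported by the elderly and care use in GP files, multiplied by an agreed mean time. Psychosocial care is one of the seven domains recorded. This measure is therefore partly covered. The time tracking form adds nothing here, because only GPs and the two nursing roles fill it in.
- The primary quality-of-life outcomes and the power calculation concern the elderly and do not depend on this list.

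**Step 5: can the gap be sized in respondents?** About 400 questionnaires with a 50% response give 400 × 0.5 = 200 returns, but the article does not split them by profession. An even spread over nine entries would be 400 / 9 ≈ 44 each, while the study practices have only 8 + 6 = 14 GPs. An even spread is therefore a poor assumption, and I give no number of missing respondents.

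**The case against.** The strongest reply is that the list was not meant as a complete roster. The sampling section selects professionals by function and region without listing functions. The knowledge questionnaire goes to the professionals involved in both groups through their employers. Since the Background counts social workers and pharmacists as health professionals, both could be reached in practice. The two lists also differ elsewhere, which suggests loose drafting in a condensed article. This stands as a caution: the text does not prove that no social worker will receive a questionnaire. It does not remove the point, because the one sentence that says who supplies data is specific, is in places more detailed than the Background, and leaves both groups out. General wording elsewhere does not override it.

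Three stronger readings are tempting but not supported.

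- **A failed social-care link would go unseen.** Other planned sources could show it: the CQ-index with added items on coherence and coordination, asked of elderly and caregivers at all three times; the nurses' diaries; the closing interviews with involved professionals; and the focus groups. Surveyed staff can also report the problem from their own side. What is missing is the social-work and pharmacy view in the quantitative rating.
- **There is no burden information on these groups.** This is true of subjective burden only.
- **Two of seven, or 29%, of the information is lost.** That fraction counts profession labels. It says nothing about respondents or precision.

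It is also fair to say that this concerns a process measure and professional outcomes, not the main comparison.

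**Conclusion.** The point holds as an inconsistency with a definite consequence. Followed as written, the plan obtains its mailed ratings of integration and relational coordination without social-work or pharmacy respondents, so ties between health and social care are judged from the health side only. Two of the seven participating professions are affected, on those ratings and on knowledge, job satisfaction and subjective burden. The loss cannot be expressed in respondents from what the article gives.

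This rests on reading the list of data suppliers as complete and on the relational coordination survey going to the same recipients. If the sponsor's working list by function already includes both groups, the remaining task is to correct the text. The change is worth making because it bears on a stated part of the research question and can still be made before the end-of-project mailing.

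**What to change.** Add social workers and pharmacists, in both the experimental and the control regions, to the list of professionals who supply data. Name their employing organizations before the end-of-project mailing, since questionnaires are distributed through employers. Adding them in one region only would make the two groups of respondents differ in composition.

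Show the degree-of-integration and relational coordination results by function, so that ties involving social work and pharmacy can be told apart from ties among the other professions.

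If the two groups are left out on purpose, say why and limit the integration conclusion to ties among the surveyed health professions.

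The cost is a modest number of extra mailings with the existing questionnaire. The respondent group becomes more mixed, which is a further reason to report by function.
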